#### 11.4.5.2 Analysis of Clinical Laboratory Data

For hematology and blood chemistry test data (quantitative values), summary statistics of the measurement and the change from baseline at each time point will be calculated, and the time course of the measurements will be graphically represented.

For urinalysis data (qualitative values), a shift table of the baseline and post-treatment value at each time point will be prepared.

#### 11.4.5.3 Analysis of Vital Signs

For body temperature, summary statistics of the measurement and the change from the final measurement before administration at each time point will be calculated, and the time course and by-subject time course of the measurements will be graphically represented.

#### 11.4.5.4 Analysis of Electrocardiographic Parameters

Not applicable.

#### 11.4.6 Blind Review

Not applicable.

### 11.5 Interim Analysis

No interim analysis will be performed in this study.

### 11.6 Sample Size Determination

Subjects with at least either a history of SARS-CoV-2 infection or vaccination with SARS-CoV-2

vaccine (Sub-population A, B and C): 690 subjects (DS-5670d group: 345 subjects, Comirnaty RTU IM group: 345 subjects)

Among those, subjects with a history of SARS-CoV-2 infection and without a history of vaccination with SARS-CoV-2 vaccine (Sub-population B): 100 subjects (DS-5670d group: 50 subjects, Comirnaty RTU IM group: 50 subjects)

Subjects without a history of SARS-CoV-2 infection or vaccination with SARS-CoV-2 vaccine (Sub-population D): Enrolled as many as possible.

#### <Rationale>

The primary objective of this study is to verify the non-inferiority in terms of blood neutralizing activity against SARS-CoV-2 (Omicron strain XBB.1.5.6) in population with at least either a history of SARS-CoV-2 infection or vaccination with SARS-CoV-2 vaccine (ABC combined). In addition, the key secondary objective is to verify the non-inferiority in terms of blood neutralizing activity against SARS-CoV-2 (Omicron strain XBB.1.5.6) in population with or without a history of SARS-CoV-2 infection or vaccination with SARS-CoV-2 vaccine (ABCD combined). Non-inferiority will have been verified if the following conditions are met simultaneously:

- The lower limit of 2-sided 95% confidence interval of GMT ratio (DS-5670d group vs. Comirnaty RTU IM group) for blood neutralizing activity against SARS-CoV-2 (Omicron strain XBB.1.5.6) at 4 weeks after study drug administration is greater than 0.67.
- The lower limit of 2-sided 95% confidence interval of the difference in seroresponse rate (DS-5670d group – Comirnaty RTU IM group) for blood neutralizing activity against SARS-CoV-2 (Omicron strain XBB.1.5.6) at 4 weeks after study drug administration is greater than –10%.

The target sample size has been set taking into account of power for the non-inferiority hypotheses, and feasibility.

#### Power for the primary objective

With the sample size of 690 subjects in the population with at least either a history of SARS-CoV-2 infection or vaccination with SARS-CoV-2 vaccine (ABC combined) and an assignment ratio (DS-5670d group : Comirnaty RTU IM group) of 1:1, and assuming that the percentage of enrolled subjects who do not contribute to immunogenicity evaluation due to reasons such as exclusion from analysis set and subjects' withdrawal from the study is 10.0%, the GMT ratio (DS-5670d group vs. Comirnaty RTU IM group) for blood neutralizing activity against SARS-CoV-2 at 4 weeks after study drug administration is 1.0, and the common standard deviation of neutralizing activity (common

Confidential

logarithmic value) is 0.533, the statistical power to detect the non-inferiority for GMT would be 98.2% at 1-sided significance level of 0.025. The standard deviation was determined based on the results of Study DS5670-103 and Study DS5670-146 to compare DS-5670a and Comirnaty IM (monovalent: original strain) in subjects aged 18 years and older.

On the other hand, assuming that the seroresponse rate for blood neutralizing activity against SARS-CoV-2 at 4 weeks after study drug administration is 80.0% in both the DS-5670d group and Comirnaty RTU IM group, the statistical power to detect the non-inferiority for seroresponse rate would be 87.2% at 1-sided significance level of 0.025.

Therefore, the power for the non-inferiority which simultaneously satisfies these primary endpoints is 85.6% ( $= 98.2\% \times 87.2\%$ ) assuming that the non-inferiority in terms of GMT and seroresponse rate are respectively independent.

### Power for the key secondary objectives

With the sample size of 790 subjects (ABC combined: 690 subjects, D: 100 subjects) in total population (ABCD combined), and assuming that the GMT ratio (DS-5670d group/Comirnaty RTU IM group) for blood neutralizing activity against SARS-CoV-2 at 4 weeks after study drug administration is 1.0, and the seroresponse rate is 80.0%, the statistical power to detect the non-inferiority for GMT would be 99.1%, and the non-inferiority for seroresponse rate would be 91.2% at 1-sided significance level of 0.025.

Therefore, the power for the non-inferiority which simultaneously satisfies these key secondary endpoints is 90.4% ( $= 99.1\% \times 91.2\%$ ) assuming that the non-inferiority in terms of GMT and seroresponse rate are respectively independent.

Meanwhile, the target sample size (100 subjects [14.5% of ABC combined]) with a history of SARS-CoV-2 infection and without a history of vaccination with SARS-CoV-2 vaccine (Sub-population B) was set to enable certain evaluation that a single dose of DS-5670d induces sufficient immunity. At the time, the feasibility was considered because the proportion of individuals aged 12 years and older who have not received the vaccine is 12.9% (based on the results of vaccination by age class published by the Office of the Prime Minister) and because 42.0% of the people aged 16 and older have anti-N antibodies that are induced by SARS-CoV-2 infection.

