## 2.2 Study Hypotheses

The primary and key secondary hypotheses are set as follows: All hypotheses will be evaluated at a one-sided 2.5% significance level. The key secondary hypothesis will be tested only if the primary hypothesis is verified.

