Multiplicity of the test associated with multiple non-inferiority hypotheses in multiple populations (ABC combined and ABCD combined) will be controlled by fixed sequence testing. First, the non-

Confidential

inferiority of the DS-5670 group to the Comirnaty RTU IM group will be tested in the ABC combined population, and only if the non-inferiority is confirmed, the non-inferiority of the DS-5670d group to the Comirnaty RTU IM group will be verified in the ABCD combined population. All hypotheses will be evaluated at a one-sided 2.5% significance level.

With reference to the PMDA notification "Principles for the Evaluation of Vaccines Against the Novel Coronavirus SARS-CoV-2, (Appendix 4) Immunogenicity-based evaluation of variant vaccines modified from parent vaccines and booster vaccines with new active ingredients," the non-inferiority margins for the GMT ratio and the difference in the seroresponse rate are set at 0.67 and -10%, respectively.

In this study, analyses will be performed twice. The first analysis will be the primary analysis of immunogenicity and safety. The primary immunogenicity and safety endpoints will be evaluated to verify the non-inferiority of DS-5670d group to Comirnaty RTU IM group once when immunogenicity and safety data are collected for all subjects for 4 weeks after study drug administration or when the study is terminated. The second analyses will be performed when or the immunogenicity and safety data for 26 weeks after study drug administration have been obtained for all subjects or the study termination.

Unless otherwise specified, continuous variables will be summarized by presenting the number of subjects, arithmetic mean, standard deviation, minimum, median, and maximum, and categorical variables will be summarized by calculating the frequency and proportion. Unless otherwise specified, baseline values from each subject will be the last observed values that are available before study drug administration. Changes from baseline (eg, change, shift table) will be analyzed in subjects whose baseline values and at least one post-treatment value are available. An outline of the statistical analyses is provided below. Statistical methods will be specified in more details in separately prepared Statistical Analysis Plan (SAP).

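### The 90.4% power given for the key secondary objective is a marginal figure that ignores the fixed-sequence gate; on the plan's own assumptions the sequential power is about 84%

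*Protocol*

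**What the plan says.** All references are to the protocol.

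- **Testing order.** Section 2.2: "The key secondary hypothesis will be tested only if the primary hypothesis is verified". Section 11.1 says that multiplicity over the two populations "will be controlled by fixed sequence testing", with A to C combined (ABC) first and A to D combined (ABCD) second. On the level it says: "All hypotheses will be evaluated at a one-sided 2.5% significance level".
- **Primary power.** Section 11.6 takes 690 subjects in ABC, 10% not evaluable, a GMT ratio of 1.0, a log10 standard deviation of 0.533 and 80% seroresponse in both arms. It obtains 98.2% for GMT and 87.2% for seroresponse, and concludes: "Therefore, the power for the non-inferiority which simultaneously satisfies these primary endpoints is 85.6" per cent.
- **Key secondary power.** Section 11.6 then takes 790 subjects (690 plus 100 in D) with the same ratio and response rate. It obtains 99.1% and 91.2%, and concludes: "Therefore, the power for the non-inferiority which simultaneously satisfies these key secondary endpoints is 90.4" per cent. The one dependence assumption stated is that the two endpoints are independent. The gate is not mentioned.
- **Size of D.** The target for Sub-population D in Section 11.6 is: "Enrolled as many as possible".

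**The concern.** The key secondary objective is to verify non-inferiority in ABCD. Under the fixed sequence this needs ABC to succeed first and ABCD to succeed next. Success on the key secondary objective is thus a subset of success on the primary one and cannot be more probable. Yet Section 11.6 gives the later step a higher power (90.4%) than the step it depends on (85.6%), under a heading that presents it as the power for the objective.

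At stake is how the whole-population claim is read. Someone taking 90.4% at face value would put the chance of missing that claim at 9.6%. Under the plan's own testing order it is about 16%.

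**Working it through.** **Inputs, all from Sections 11.1 and 11.6.** One-sided level 0.025; margins 0.67 (GMT ratio) and −10 points (seroresponse); log10 standard deviation 0.533; true ratio 1.0; 80% against 80%; 690 subjects in ABC and 790 in ABCD, 1:1; 10% not evaluable. The key secondary paragraph does not restate the 10%, but its figures reproduce only with it. Evaluable per arm: 690 × 0.9 / 2 = 310.5 and 790 × 0.9 / 2 = 355.5.

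**Step 1. Reproduce the plan's component powers.**

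- GMT: power = Φ(−log10(0.67) / (0.533 × √(2/n)) − 1.96), with −log10(0.67) = 0.1739.
  - n = 310.5: Φ(0.1739/0.04278 − 1.96) = Φ(2.106) = 98.2%.
  - n = 355.5: Φ(0.1739/0.03998 − 1.96) = Φ(2.391) = 99.2%. With the t distribution it is 99.1% to 99.2%, against 99.1% stated.
- Seroresponse: the Farrington-Manning (constrained variance) formula gives 87.2% and 91.2%, as stated. The unpooled variance gives 87.6% and 91.5%.
- Products: 0.982 × 0.872 = 0.856 and 0.991 × 0.912 = 0.904.

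Both stated joint powers reproduce. The second contains no term for the gate, so 90.4% is the marginal power of the ABCD comparison.

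**Step 2. Sequential power under the plan's assumptions.** The ABC subjects are contained in ABCD. For each endpoint the two test statistics are therefore approximately bivariate normal with correlation √(690/790) = 0.935. Feeding in the protocol's own marginal powers:

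| Endpoint | ABC alone | ABCD alone | Both |
|---|---|---|---|
| GMT | 98.2% | 99.1% | 98.0% |
| Seroresponse | 87.2% | 91.2% | 86.1% |

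With independent endpoints, 0.9805 × 0.8608 = 0.844. **Sequential power is 84.4%.** With unpooled variance it is 84.9%, and a simulation of 400,000 trials gave 84.8%. The chance of missing the claim is 100 − 84.4 = 15.6%.

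**Step 3. Ceilings.**

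- With independent endpoints, the sequential power cannot exceed the primary power of 85.6%.
- Without independence, the primary power cannot exceed that of its weaker endpoint, so the ceiling is 87.2%.
- With assumed endpoint correlations of 0.3 to 0.8 and the protocol's marginal powers, the sequential power runs from 84.8% to about 86%. With unpooled variance the range is 85.3% to 86.3%.

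No case reaches 90.4%.

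**Step 4. What the gate costs.** Given primary success, the ABCD test succeeds with probability 0.844/0.856 = 98.6%. Almost all of the shortfall is the risk of missing the primary itself.

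**The case against.** The strongest reply is that nothing has been miscalculated. Section 11.6 gives its inputs, its method and its independence assumption, and every figure reproduces. Reporting the power of each hypothesis separately is common in a fixed sequence. The gate is stated openly in Sections 2.2 and 11.1, and the 85.6% stands directly above. The primary power is what supports the 690 subjects, and 90.4% sets no recruitment number.

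Most of this stands. It rules out calling the figure an arithmetic error, and it limits the consequences. It does not supply the missing label: the figure is headed as the power for the key secondary objective, and that objective can be verified only through the gate.

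Three stronger readings are tempting, and the protocol does not support them:

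- **That 85.6% is an absolute cap, whatever the size of D.** It holds only under independence of the endpoints. Both use the week-4 titre, so positive correlation is plausible, and the cap free of that assumption is 87.2%.
- **That 100 subjects in D contradicts the open-ended target, or treats all 100 as evaluable.** The 100 is disclosed as an input to the power calculation, which need not be a recruitment target. The stated powers reproduce only with 10% attrition on all 790, so D contributes about 90 evaluable subjects.
- **That the power is lower still because D responds less well to DS-5670d than to the comparator.** The protocol gives no treatment effect for D, so any such figure would be a supposition unrelated to the gate.

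**Conclusion.** The point holds as a mislabelled power. The 90.4% is a correct marginal power for ABCD, shown as the power for an objective that the design tests only after another has succeeded. The sequential power is about 84% (84.4% from the protocol's own component powers, up to 84.9% with a different variance formula), some 6 points lower. This assumes a GMT ratio of 1.0 and 80% seroresponse throughout, 100 enrolled in D, 10% attrition and independent endpoints. With assumed positive correlation between endpoints the gap narrows to about 4 to 6 points but does not close.

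A reader might infer that the trial is too small or that the testing procedure is unsound. Neither follows: the 690 rests on the primary power, which reproduces, and the gate protects the type I error as intended. This should be fixed, but it is not critical, because only the stated key secondary power changes.

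**What to change.** In Section 11.6, under the power for the key secondary objectives:

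1. Label 99.1%, 91.2% and 90.4% as marginal powers of the ABCD comparison that ignore the testing order.
2. Add the probability that ABC and then ABCD both succeed: about 84% with 100 enrolled in D and independent endpoints. If a ceiling is quoted, give 85.6% with the independence condition, or 87.2% without it.
3. Say that 100 subjects in D is a planning assumption, because D has no recruitment target, and that the 10% attrition is applied to all 790.

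The cost is a few sentences and a key secondary power about 6 points less favourable. Sample size, margins, analysis sets and testing order stay as they are.

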## 11.7 Statistical Analysis Process

Statistical analysis will be performed by the sponsor or the CRO in accordance with the protocol and the SAP. The SAP represents statistical methods and definitions for analyzing efficacy and safety data, and also describes methods for summarizing other data, including disposition, demographic and other baseline characteristics of subjects, exposure to the study drug, and concomitant medications. The SAP will also include a description of how missing, unused, and spurious data will be addressed.

Confidential

To maintain the integrity of statistical analysis and study conclusion, the SAP will be finalized and fixed before unblinding.

All statistical analyses will be performed using SAS Version 9.4 or later (SAS Institute).

## 12. DATA INTEGRITY AND QUALITY ASSURANCE

The head of the study site and the investigator will permit monitoring by the sponsor, audits, IRB review, and regulatory inspections by providing direct access to all study-related records including source documents. The sponsor will conduct monitoring and audits and directly access study-related records including source documents at the study site to confirm that the study has been appropriately conducted and the data reliability is properly assured. The sponsor will discuss with the investigator in advance regarding the procedures for direct access to source documents.

### 12.1 Monitoring and Inspections

The sponsor, CRO monitors, and regulatory authority inspectors are responsible for contacting the investigator and visiting the study site for the purpose of inspecting the facilities and, upon request, inspecting the various records of the study (eg, eCRFs, source data, other pertinent documents).

The verification of adherence to the protocol, completeness, accuracy, and consistency of the data, and adherence to ICH-GCP and local regulations on the conduct of clinical research will be accomplished through a combination of onsite visits by the monitor and remote review of study data. The frequency of the monitoring visit will vary based on the activity at each study site. The monitor is responsible for inspecting the eCRFs and ensuring the completeness of the study essential documents. The monitor will have access to subject medical records and other study-related records needed to verify the entries on the eCRFs. More details are provided in the Monitoring Plan.

The monitor will inform the investigator of violations of the protocol, standard operating procedures (SOPs), GCP, and applicable regulations, and ensure that appropriate actions to prevent their recurrence are taken and documented.

The investigator should agree to take actions satisfactory to the sponsor in cooperation with the monitor when any problem is detected during the process of monitoring, and ensure that they are documented.

In accordance with ICH-GCP, local regulations and the sponsor's audit plans, this study may be selected for audit by representatives from the sponsor. Audit of study site facilities (eg, pharmacy, drug storage areas, laboratories) and review of study-related records will be conducted to evaluate the study conduct and compliance with the protocol, ICH-GCP, and applicable regulatory requirements. The investigator should respond to audit findings. In the event that a regulatory authority informs the investigator that it intends to conduct an inspection, the investigator should notify the sponsor immediately.

### 12.2 Data Collection

#### 12.2.1 Preparation of Case Report Forms

The sponsor will supply eCRFs. The investigator or subinvestigator will ensure that an eCRF is completed for each subject who signed the ICF and underwent any screening procedure. If the subject

is not administered the study drug, the reason must be recorded in the eCRF. All data collected during the study must be recorded in individual, subject-specific eCRFs. CCG will be provided by the sponsor. All entries and corrections to eCRFs will be automatically recorded as an audit trail in the EDC system. The eCRF should be kept current to enable the monitor to review the subject's status throughout the course of the study.

The eCRF must be completed, reviewed, and signed or e-signed by the investigator. The investigator will sign and date the eCRF via the EDC system's electronic signature. These signatures will indicate that the investigator inspected or reviewed the data in the eCRF, data queries, and site responses, and agrees with the content.

Easy-to-understand vocabulary and terminology must be used for all the information and other materials to be used by subjects and study staff in the study.

### 12.2.2 Entry Precautions for the Completion of Case Report Forms

In this study, the eCRF (completed by the investigator), clinical laboratory data report (prepared by the central laboratory), electronic diary (completed by subjects or legal representatives), verification report documented by telephone contacts, and immunogenicity measurement result report (prepared by the institution for immunogenicity measurement) will be prepared.

In this study, eCRFs will be electronically completed using a system (EDC System). The eCRF (including audit trail) will be completed for each subject and that signed by the investigator will be handled as the original. A validated EDC system will be used.

The eCRF will be created for subjects who provided informed consent.

### 12.2.3 Format of the Electronic Diary

Electronic diary data will be collected using an application (data entry system) installed on the electronic clinical outcome assessment (eCOA) device. The electronic diary entry account will be prepared for each subject. An electronic diary entry device will also be lent to them, if necessary. The subject or legal representative will answer all question items in the electronic diary, and the investigator will review the answers using the EDC system. A validated eCOA entry system will be used.

## 12.3 Data Management

Each subject in the database will be identified by a unique subject identifier as defined by the sponsor.

To ensure the quality of clinical data across all subjects and study sites, a clinical data management review will be performed on subject data according to the specifications given to the sponsor and the CRO. Data will be vetted both electronically and manually for eCRFs and the data will be electronically vetted according to the data rules programmed within the application. Queries

generated by the rules and raised by reviewers will be generated by the EDC system. During this review, subject data will be checked for consistency, completeness, and any apparent discrepancies.

Data received from external sources such as the central laboratory will be reconciled with the clinical database.

SAEs in the clinical database will be reconciled with the safety database.

All AEs entered in eCRFs will be coded using MedDRA.

Medical history/complications will be coded using MedDRA.

Concomitant medications will be coded using the WHO Drug Global B3 format.

## 12.4 Study Documentation and Storage

The investigator will maintain a signature list of appropriately qualified persons to whom he/she has delegated study duties.

The investigator will maintain a confidential screening log that includes information of all potential study candidates and the date and outcome of the screening process.

The investigator will be expected to maintain an enrollment log of all subjects enrolled in the study, including their assigned study numbers.

The investigator will maintain a confidential subject identifier list. This confidential list of names of all subjects assigned study numbers on enrolling in the study allows the investigator to reveal the identity of any subject when necessary.

Source documents are original documents, data, and records from which the subject's eCRF data are obtained. These include but are not limited to hospital records, medical records, clinical laboratory and pharmacy records, electronic diaries, microfiches, X-rays, and correspondence.

Records of subjects, source documents, data correction forms, eCRFs, electronic diaries, inventory of study drugs, regulatory documents (eg, protocol and amendments, IRB/EC correspondence and approvals, approved and signed ICFs, investigator's agreement, study drug receipts, distribution and return records), and other sponsor correspondence pertaining to the study must be kept in appropriate study files at the study site (Trial Master File [TMF]). Source documents include all recordings and observations or notations of clinical activities and all records necessary for the evaluation and reconstruction of the clinical study. These records will be retained in a secure file for the period required by the facility or the study site. Prior to transfer or destruction of these records, the sponsor must be notified in writing and be given the opportunity to further retain such records.

Entries in the eCRF, if the following items are entered directly in it (ie, there are no previously written or electronically recorded data) and all entries in the electronic diary will be considered source data:

- 1) Free description column in each item (comment column, etc.)
- 2) Entries of "No" or "Not done" in each item
- 3) Purpose of use of concomitant medications and therapies

Confidential

- 4) The severity, seriousness, date of outcome, and causality with study drug regarding AEs
- 5) Reasons for withdrawal

